### **Intervention outcome measures**

During the intervention study, questionnaires and 3-day food records will be completed by all adult subjects, and fat biopsies and fasting blood samples will be taken, anthropometric measurements (weight, body composition, etc) and 24h urine collections will be made and oral glucose tolerance tests (OGTT) will be performed. Some adult subjects are involved in specific sub-studies (described in Section 6).

The overweight children (aged 5 - 18) will also complete 3-day dietary records, and will have blood and urine samples taken (but not fat biopsies) for measurement of safety factors and certain hormones, and will also undergo anthropometric measurements (height, weight etc). Normal weight children will undergo anthropometric measurements and have blood and urine samples taken for measurement of safety factors only. All these measures and the visits planned are described in more detail ahead (Section 9).

### **Compliance monitoring procedures**

Before, during and after the intervention, compliance assessment is carried out to evaluate and ensure adherence to the dietary regimens. In addition to self-reported dietary records (adults and children), blood and urinary samples will be taken (adults only) to assure and monitor the adherence to the dietary regimens.

### **Duration of the study**

The study will begin recruitment of families by September 2005 and will start in January 2006 (LCD diet), with a staggering period of about 12 weeks. The 12 months intervention period will be finished in around June 1, 2007 and the final 24-month follow up visit will complete the study in around June 2008.

### **Ethics**

The study will be performed according to the latest version of the Declaration of Helsinki, the UN Convention on the Rights of the Child and the Current International Conference on Harmonization

---

 CID 2 for children will take place in week 4

(ICH) guidelines. Wherever possible, the study will be performed according to the current Good Clinical Practice (GCP) guidelines. An application will be submitted to the regional Ethics Committee and the study will not be undertaken without a positive statement from the committee regarding the study. All subjects (including children where possible) must give verbal and written informed consent before they can be entered into the study.

## **Insurance**

The subjects will be insured via the public patient insurance. 2. LIST OF ABBREVIATIONS

|          |                                              |
|----------|----------------------------------------------|
| AE       | Adverse Event                                |
| ANACOVA  | Analysis of Covariance                       |
| BP       | Blood Pressure                               |
| BMC      | Bone Mineral Content                         |
| BMI      | Body Mass Index                              |
| BMR      | Basal Metabolic Rate                         |
| CID      | Clinical Investigation Day                   |
| CVD      | Cardiovascular Disease                       |
| DBP      | Diastolic Blood Pressure                     |
| DiOGenes | Diet, Obesity and Genes                      |
| DEXA     | Dual-energy X-ray Absorptiometry             |
| DLW      | Doubly labelled water                        |
| FM       | Fat Mass                                     |
| GCP      | Good Clinical Practice                       |
| GI       | Glycaemic Index                              |
| ICH      | International Conference on Harmonization    |
| IGF-1    | Insulin-like Growth Factor-1                 |
| IGFBP-3  | IGF Binding Protein-3                        |
| LCD      | Low Calorie Diet                             |
| LTM      | Lean Tissue Mass                             |
| OGTT     | Oral Glucose Tolerance Test                  |
| RDA      | Recommended Daily Allowance                  |
| RTD      | Research, Technological and Development      |
| RVAU     | Royal Veterinary and Agricultural University |
| SAE      | Serious Adverse Event                        |
| SBP      | Systolic Blood Pressure                      |
| SD       | Standard Deviation                           |
| TBW      | Total Body Weight                            |
| VAS      | Visual Analogue Scales                       |

## 2. BACKGROUND

Obesity is generally regarded to be the most prevalent nutritional disorder in Europe. As the prevalence of obesity has increased, so have the number of clinical and scientific studies aimed at determining which dietary components are most efficacious for promoting and sustaining weight loss. A large body of evidence has demonstrated that a reduction in dietary fat content under *ad libitum* conditions can produce a modest but clinically important weight loss in 6-12 months (3), and in combination with a slight increase in physical activity can prevent 58% of new cases of type 2 diabetes in high risk obese subjects (4). It is clear, however, that the non-fat component of the diet is also critically important.

The glycaemic index (GI) of carbohydrates has been demonstrated to have importance for cardiovascular risk factors and glycaemic control in diabetics, and has been suggested to play a role in appetite control (5). A number of studies, and several popular diet books, attribute passive over-consumption of energy to a diet with a high GI, and suggest that replacing high GI foods with similar low GI foods can prevent this or lead to a greater loss of fat compared to lean body tissue (5;6). The literature, however, is conflicting. Systematic reviews are equivocal and point to many negative studies that suffer from lack of dietary compliance and standardisation, and lack of statistical power to detect weight changes of clinical relevance and particularly of public health relevance (7;8). It is also pertinent to note that even the concept of GI has been questioned because of its poor reproducibility (GI is affected by fruit ripeness, food particle size, type of a particular food, food processing and cooking methods, for instance) (8). Furthermore, most GI studies to date are of short duration and have been carried out with single food items as opposed to mixed meals. The current study will take these shortcomings into consideration.

*Ad libitum* diets with high protein content have been shown to enhance satiety (9;10) and increase thermogenesis (11) in a number of smaller studies, and also produce better weight control and weight loss than diets in which the protein is replaced by carbohydrate (12;13). These high-protein diets are challenging the current recommendations (14) and need to be evaluated for efficacy and safety in a large, long-term, strictly controlled intervention trial (13). The Institute of Medicine (15) has recently increased the recommended acceptable daily protein intake for adults to 10-35% caloric intake and for children (aged 4-18) to 10-30%. A previous 6-month study found that a fat-reduced diet with high compared to normal protein enhanced weight loss and provided a greater reduction in intra-abdominal fat stores (12). However this pilot study did not have the statistical power to assess weight differences between groups after 12 months due to inadequate numbers of subjects (16). Moreover, adverse effects of high protein diets on renal function in healthy individuals have not been clearly established to date, and effects on bone are unclear (13). The safety and tolerability of a high protein diet in different age groups thus requires clarification, in particular in children; this will be exerted in the current study.

The rapid increase in childhood obesity which currently affects all European countries is of particular societal concern today. This study is novel because it focuses on the whole family. The aim is to identify the diet most effective for protection against weight gain and weight regain in a susceptible population of obese and overweight individuals and their children. Investigating the diet within the whole family should encourage overweight children to lose weight; indeed some studies have demonstrated that the family based approach to body weight management is most effective for weight loss. In addition the diet most beneficial for risk factors of CVD and type-2 diabetes also

requires clarification (5;14). The uncertainty about the optimal diet composition for the prevention and treatment of obesity is a public health problem which needs to be addressed by a large long-term randomized intervention trial. This is the background for the proposed dietary intervention study, which hopefully will contribute to the knowledge in this area and provide valid evidence that may help decision makers to make appropriate dietary recommendations.

### 3. DESIGN

This randomised controlled dietary intervention study will involve approximately 50 families in Denmark (75 initially screened, thus allowing for drop-out). Families will comprise at least 1 obese parent ( $\text{BMI} > 30 \text{ kg/m}^2$ ) and 1 overweight(2) child ( $\text{iso-BMI} > 25$ ); the other parent will be overweight ( $\text{BMI} > 28 \text{ kg/m}^2$ ). After screening (see Sections 7.1 & 7.2), all adult subjects will initially undergo an 8-week LCD weight loss diet. This will be followed by a 12 months *ad libitum* dietary intervention study (see below), consisting of a 6-month SUPERMARKET period and a 6-month DIETARY INSTRUCTION period. Subsequently there will be a 24-month follow-up after 12 months free-living with no dietary intervention (see Study Flow Diagram, Section 2).

CID 1 will take place in the 3 weeks prior to the LCD diet. This will include (adults) anthropometric measurements, BP, blood sample and 24-h urine collection, fat biopsy, OGTT and analysis of body composition using dual-energy x-ray absorptiometry (DEXA), and completion of lifestyle/behavioural questionnaires. For all children, CID 1 will include anthropometric measurements and blood sample/urine collection for safety measures, with additional measures of body composition (DEXA/bioimpedance) and blood samples for hormone analysis for overweight children only.

A number of subgroup investigations (adults only) will also be initiated in the 3 weeks prior to the LCD diet:

Subgroup a: This subgroup will complete a 7-day food record and undergo basal metabolic rate (BMR) and doubly labelled water (DLW) measurements, have physical activity measured by use of a pedometer and have a meal test.

Subgroup b: This sub-group will have one extra fat-biopsy taken on the 3rd day into the LCD diet.

#### 1. 8 week LCD dietary period

The energy restricted LCD diet (for adults only) will consist of 800-1000 kcal/d and the target macronutrient composition of the diet will be 15-20% of total energy from fat, 35-40% from protein and 45-50% from carbohydrate. No energy restriction will be imposed for the children in the enrolled families. During this period, subjects will attend approx. 6 group meetings at the Department where their body weight, adverse events (AE) and concomitant medication will be registered and dietary and behavioural instructions will be given.

Before entering intervention period 1, adult subjects visit the Department for CID 2. This will again include anthropometric measurements, BP, blood sample and 24-h urine collection, fat biopsy, OGTT, analysis of body composition (DEXA scan), and completion of lifestyle/behavioural questionnaires. Families where at least one parent achieves a  $>8\%$  weight loss will be randomised to one of the 5 dietary arms.

Subgroup a will complete a 7-day food record and undergo BMR and DLW measurements, have physical activity measured by use of a pedometer and have a meal test.

## **2. 6 months dietary intervention period 1 (SUPERMARKET period)**

Families in which at least one parent has achieved an 8% loss of initial body weight will be randomised to one of 5 dietary arms (see Table 1), including a control group. Subjects enrolled in the 4 intervention groups will be expected to get most of their foods free of charge in the supermarket for the first 6 months of the intervention. The on-site supermarket has fresh, shelved and frozen products, separated according to the dietary design. All food items will be bar-coded and a dietician will scan the barcodes of all the chosen items to monitor macronutrient composition of the diet and will assist in altering the selection to meet the prescribed macronutrient composition. Each food item scanned will be registered in a database in the shop. The calculated energy content of the chosen groceries will not be made known to the subjects. The control group will be instructed to continue their habitual dietary intake whilst shopping in ordinary food shops (thus their food will not be free).

Families in all intervention groups will receive careful, intensive and regular dietary and behavioural guidance during both intervention periods 1 and 2, although the control group will not receive advice regarding dietary composition. The dietary instruction will include family sessions, where instruction will be given to the whole family, including children. The dietician will advise on weight control and reinforce the diet composition through recipes, cooking advice, and behaviour modification in group (several families) and individual meetings (one family). Subjects will be given oral and written instructions relating to the five intervention groups based on an exchange system. The aim is to reach the required macronutrient composition on a daily basis. Hence, individual meals (breakfast, lunch, dinner) may not necessarily have the designated macronutrient composition. During intervention periods 1 and 2, weight maintenance is attempted, though further weight reduction will be allowed, i.e. in all 5 groups, the diet intervention is carried out with less emphasis on the calorie content of the diet (which is *ad libitum*) or the calorie density of the diet, but with major emphasis on adherence to the diet prescribed. Hence, during both periods 1 and 2 it is the diets' ability to satisfy and to regulate appetite and body weight that will be tested.

In week 4 of period 1, the children will visit the Department for their CID 2. This will include (all children) anthropometric measurements and blood sample/urine collection, with additional measures of body composition (DEXA/bioimpedance) for overweight children only.

Before entering intervention period 2, adults and children visit the Department for CID 3, including (adults) anthropometric measurements, BP, blood sample and 24-h urine collection, fat biopsy, OGTT and analysis of body composition (DEXA scan). Measures for children include (all children) anthropometric measurements and blood sample/urine collection, with additional measures of body composition (DEXA/bioimpedance) for overweight children only.

Subgroup a will complete a 7-day food record and undergo BMR and DLW measurements, and have physical activity measured by use of a pedometer.

## **3. 6 months dietary intervention period 2 (DIETARY INSTRUCTION period)**

Families will be followed for another 6-month intervention period (Period 2), although free food will not be supplied and families will be expected to shop in ordinary supermarkets. Throughout this period the subjects will again receive dietary/behavioural instructions. Families will be encouraged to follow the dietary regimens in accordance with their randomization. Also during this phase, weight maintenance is attempted, though further weight reduction will be allowed. At the end of intervention period 2, CID 4 will take place. This will include (adults) anthropometric measurements, BP, blood sample and 24-h urine collection, OGTT and analysis of body composition (DEXA scan). For all children, CID 4 will include anthropometric measurements and blood sample/urine collection, with additional measures of body composition (DEXA/bioimpedance) for overweight children only.

## 4.1 DIETARY GROUPS

*Table 1: Dietary groups during the intervention study.*

|                | Low glycaemic index | High glycaemic index |
|----------------|---------------------|----------------------|
| Normal protein | 1                   | 2                    |
| High protein   | 3                   | 4                    |
| Control        | 5                   |                      |

1. 25-30% of energy from fat, 10-15% from protein and 57-62% from low GI carbohydrates.
2. 25-30% of energy from fat, 10-15% from protein and 57-62% from high GI carbohydrates.
3. 25-30% of energy from fat, 23-28% from protein and 45-50% from low GI carbohydrates.
4. 25-30% of energy from fat, 23-28% from protein and 45-50% from high GI carbohydrates.
5. Control diet, concordant with the family's habitual diet.

High protein content is defined as 25% of energy intake (range 23-28%); although the long term safety of a high protein diet may not be fully evaluated, these percentages were used in a previous 6-month study of high protein intake(12) and are within the acceptable range for both children (10-30%, children aged 4-18) and adults (10-35%) (15). Thus the lower level for protein of 12% of energy intake (range 10-15%) is also within the normal Recommended Daily Allowance (RDA) range for children and adults (15). The protein sources will be primarily of animal origin, such as lean meat and low fat dairy products, but will also include vegetable proteins, such as pulses (beans, lentils and peas), which are usually quite inexpensive.

High GI is concordant with the habitual European diet (5) but may also be linked with increased risk of obesity, therefore the potential adverse effects of this type of diet will be examined within the study. The glycaemic level of the diet will be determined on the basis of international GI tables (17).

## 4.2 METHOD OF ASSIGNING FAMILIES TO DIETARY GROUPS

The eligible families will be allocated to a dietary intervention group using a simple block randomization procedure with centre, number of obese parents in the family and BMI (greater or less than 34, screening value) as stratification criteria by a third party with no knowledge of the

subjects that may affect the outcome of the study. Approx. 11 families are randomized to each of the 5 dietary intervention groups. The outcome in the dietary intervention groups will be compared to each other and to the control group.

Approx. 6 subjects in each dietary group (3 men and 3 women) will be randomized to **Subgroup a** (7-day food record, BMR and DLW measurements, physical activity using pedometers, meal test). Approx. 7-10 subjects in each dietary group will be randomized to **Subgroup b** (extra fat biopsy day 3 into LCD diet).

Participation by (adult) subjects in the sub-groups is entirely voluntary and separate information sheets and consent forms will be signed.

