### **8.2 STATISTICAL PROCEDURES**

All statistical analysis described in this protocol will be performed by the investigator. All analysis and tabulations will be performed using the latest release of the SAS® or SPSS software or similar statistical software. Appropriate descriptive statistics will be presented for each variable; n=number of patients, mean, median, SD and min-max for continuously distributed variables, and rates and percentages for categorical variables. Statistical tests will be performed using 5% as the nominal level of significance and interval estimates will be constructed using 95% as the level of confidence. Statistical and analytical methods, and sample size considerations are discussed in the following sections. The investigator will make the decisions regarding subjects, or individual values belonging to a patient, to be excluded from the analysis. Subjects will only be excluded from the efficacy analysis when the uses of these are considered a protocol violation, putting the scientific aspects of the trial at risk. The variables that will be statistically tested are given in the Sections concerning primary and secondary variables.

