### 8.2.5 PRIMARY HYPOTHESIS

The following primary hypothesis can be applied:

H0: The 1o outcome (weight, etc) is equal in the intervention groups at week 26 and week 52, when controlling for the value in CID2 (adults) or CID1 (children).

vs.

H1: The 1o outcome is different in the intervention groups at week 26 and week 52, when controlling for the value in CID2 (adults) or CID1 (children).

The changes in continuously distributed variables from baseline to week 26 and week 52 within treatment groups will be tested with the paired t-test or the Wilcoxon-Signed-rank test, depending on distribution (all tests two-sided).

All categorical variables will be expressed in contingency tables and analyzed using Fisher's exact test. Survival analysis using the Kaplan-Meier plot and the log-rank test will be used to investigate time to subject withdrawal.

All null hypotheses comparing groups assume equality between the treatment groups while the alternative hypotheses assume that there is a difference (two-sided). All within-group null hypotheses assume no change from baseline to week 26 or week 52 while the alternative hypotheses assume that there is a change (two-sided).

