### **8.2.7 SAMPLE SIZE ESTIMATION**

The primary aim of the study is to investigate the long-term efficacy in terms of change in body weight from baseline to study end. The sample size for the proposed study was chosen to provide sufficient power to detect differences in 26-week weight regain (for primary participants) due to the effects of the different diets. The sample estimation is based on the difference between the intervention and control groups regarding weight change (kg) from baseline to week 26. In the null hypothesis we assume that the interventions groups 1 - 4 are of equal weight at week 26 compared to baseline, while the alternative hypothesis assumes that there exists a difference in weight between the treatment groups. By this covariate method we are able to test the change from baseline to week 26 while controlling for between-group differences in the baseline value.

It is anticipated that weight differences will be smallest between the low vs. high GI diets compared to the low protein vs. high protein diets. Hence the sample size has been calculated on the basis of a previous intervention study on GI (18), which found a non-significant difference in body weight change of 0.6 kg between groups using the unpaired t-test. We assume a 0.4 kg higher weight loss based on 6-month treatment, compared to the 10-week previous intervention study (18). Thus we consider that a weight loss difference of 1 kg is a clinically relevant weight loss and a priori we assume a SD of 2.01 kg.

When assuming a difference between control and intervention group of 1.0 kg (SD 2.5 kg), at least 80% statistical power and a significance level of 5%, N=125 participants per group are required (unpaired t-test). In this model, any effect size above 0.72 kg gives a power of more than 80%.

As most other studied variables in the study are secondary objectives and because the outcome of most of these variables are not easily comparable to previous studies due to the novel design of the study, there are no calculations on sample size for variables other than the primary efficacy parameter, which is weight change to week 26.

Thus, in terms of final outcome, it is accepted that post-hoc analysis will identify that not all measures of other primary or secondary outcomes will necessarily have had the appropriate sample size.

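### Protein-by-GI factorial: no protein or GI main effect is named, the 1.0 kg planning effect changes contrast, and several main outcomes at two visits share an unallocated 5%

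*Protocol*

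**What the plan says.** Table 1 in Protocol 4.1 crosses normal or high protein with low or high GI (groups 1-4) and adds a control arm (group 5). On comparisons, 4.2 states: "The outcome in the dietary intervention groups will be compared to each other and to the control group". Section 8.2.1 sets the objective as estimating the effects of high or normal protein and high or low GI against a control diet.

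The sample-size section, 8.2.7, starts from GI: "It is anticipated that weight differences will be smallest between the low vs. high GI diets compared to the low protein vs. high protein diets". It takes a 0.6 kg difference from an earlier 10-week GI study, adds 0.4 kg for longer treatment, and arrives at 1.0 kg. It words its null about groups 1-4. The calculation then begins "When assuming a difference between control and intervention group of 1.0 kg" and gives 125 per group by unpaired t-test with SD 2.5 kg.

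On what is primary, 8.2.7 refers to "the primary efficacy parameter, which is weight change to week 26". Section 8.2.2, however, lists four kinds of adult main outcome: weight loss maintained, body composition, proportions above three thresholds, and drop-out. It adds a separate set for children. Section 8.2.4 compares the main outcomes by ANCOVA at weeks 26 and 52, and the alternative in 8.2.5 is that the primary outcome "is different in the intervention groups at week 26 and week 52". On the error rate, 8.2 says: "Statistical tests will be performed using 5% as the nominal level of significance". No order of testing or division of the 5% is given.

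**The concern.** Three decisions that belong together do not agree.

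1. **Contrast.** The design asks two factorial questions, but no test of either factor is named. The only diet interaction terms, in 8.2.3, are with biological or psychological traits.
2. **Planning effect.** One sample size is tied to three contrasts: low versus high GI (source of the 1.0 kg), equality among groups 1-4 (the null), and control versus intervention (the calculation). The 1.0 kg has no stated basis for the last. In period 1 the control families also buy their own food and get no advice on diet composition (section 3), so that contrast carries more than macronutrient composition.
3. **Primary endpoint.** One section names a single parameter, while others give several outcomes at two visits the same standing.

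At stake are the false-positive rate behind any result called primary and the precision on protein and GI.

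**Working it through.** **Inputs.** Difference 1.0 kg, SD 2.5 kg, 80% power, 5%, 125 per group (8.2.7); two-sided tests (8.2.5); five arms (4.1); four kinds of adult main outcome (8.2.2); two visits (8.2.4, 8.2.5). Correlations between outcomes and visits are not in the protocol and are assumed below.

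**The plan's own figure.** n per group = 2 × (1.960 + 0.842)² × SD² / difference² = 2 × 7.85 × 6.25 / 1 = 98.1, so 99 (100 with the exact t-test). The stated 125 equals 100 / 0.80, which implies 20% drop-out, a rate the calculation does not state. The 0.72 kg quoted as detectable fits the section's other SD: 2.802 × 2.01 × √(2/125) = 0.71 kg (0.715 with the t-test). For SD 2.5 it is 0.89 kg. I therefore use 125 and SD 2.5.

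**Precision on protein or GI.** Detectable effect = 2.802 × SD × √(2/n per side).

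- One arm against one arm, 125 v 125: 2.802 × 2.5 × √(2/125) = 0.886 kg (0.89 with the t-test). Power for 1.0 kg is 88%.
- Pooled main effect, 250 v 250: 2.802 × 2.5 × √(2/250) = 0.626 kg (0.63 with the t-test). Power for 1.0 kg is 99%.
- The ratio is √2 = 1.41. It applies only to the protein and GI questions, and only if there is no material interaction.

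**Cost of controlling error over two main effects.** With 2.5% each, the standard error is 2.5 × √(2/250) = 0.2236 kg, and power for 1.0 kg is Φ(1/0.2236 − 2.241) = Φ(2.231) = 98.7%. Holm is never less powerful than this split.

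**Power for the interaction.** For a 1 kg difference of differences, the standard error is 2.5 × √(4/125) = 0.447 kg. Power is Φ(1/0.447 − 1.960) = Φ(0.276) = 61%.

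**Family-wise error when all groups are equal, each test at 5%.**

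| Reading | Family-wise error |
|---|---|
| All 10 pairs, one outcome, one visit | 28.6% (studentized range; 28.4% by simulation) |
| Six pairs within groups 1-4, one outcome, one visit | 20% |
| Four groups v control, one outcome, one visit | 16% |
| One omnibus test, weight only, two visits | 7-9% |
| One omnibus test, four outcomes, two visits, correlated | 17-28% |
| Same eight tests if independent | 1 − 0.95⁸ = 33.7% |

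The correlated rows assume a between-visit correlation of 0.5 to 0.9 and, for four outcomes, a between-outcome correlation of 0.5 to 0.8. They treat every outcome as continuous and count the three weight-loss thresholds as one outcome. Fisher's exact test, planned in 8.2.5 for categorical variables, is conservative and would lower these figures somewhat.

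**The case against.** A reader might infer that the protocol prescribes ten unadjusted pairwise tests and so throws away half the factorial data. It does not. The sentence in 4.2 is descriptive and sits in the randomisation section. ANCOVA with a group factor allows factorial contrasts, and the null in 8.2.5 can be read as one global test. The protocol is silent on main effects; it does not exclude them. The 29% and the 0.89 kg are therefore conditional on arm-against-arm testing.

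A reader might also infer that no primary result could claim 5%. If week-26 weight change were the sole primary outcome and one omnibus test the sole test, the rate would be 5%. Section 8.2.7 points that way, but 8.2.2, 8.2.4 and 8.2.5 do not. Contrast coding and adjustment are often left to an analysis plan; the conflict over what is primary, and the change of contrast in 8.2.7, are in the protocol's own text.

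Nor do the local numbers, about 11 families per group in 4.2, show that the sized trial is underpowered. They describe one centre, while the Synopsis describes 350 families in eight countries.

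Two objections stand and shape the fix. Comparison with control is a stated objective (8.2.1), and the Background seeks the most effective diet, so arm-level contrasts must stay. And an interaction is plausible: carbohydrate supplies 57-62% of energy at normal protein but 45-50% at high protein (4.1), so GI acts on different amounts of carbohydrate.

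**Conclusion.** The point holds in a limited form. The protocol contradicts itself on what is primary, names no test for either factor, and applies a GI-derived effect to a control comparison. With the main outcomes and visits as listed, family-wise error exceeds 5% even on the omnibus reading: roughly 17-28% under the assumed correlations, and 34% only under independence. If protein and GI are tested arm against arm, the detectable effect is 0.89 kg instead of 0.63 kg, assuming SD 2.5 kg, 125 per group and no material interaction.

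This is lost precision, not a failed power target, since pairwise power for 1.0 kg is 88%. All power figures ignore correlation between parents randomised as one family, which would change the absolute values.

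**What to change.** 1. Reconcile 8.2.2, 8.2.4, 8.2.5 and 8.2.7 so that adult weight change from CID 2 to week 26 is the single primary endpoint.
2. Name two primary contrasts within groups 1-4: protein (3+4 v 1+2) and GI (1+3 v 2+4), with Holm across them. Report the interaction estimate with its confidence interval, and the four cell means.
3. Keep the control comparisons as pre-specified key secondary contrasts with their own multiplicity control. Note that in period 1 they also differ in free food.
4. Make week 52, body composition, the proportions and drop-out secondary, and state where the children's outcomes sit.
5. State in 8.2.7 which contrast the 1.0 kg applies to.

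**Cost.** No added participants, visits or procedures. Power for 1.0 kg on each main effect stays at 98.7% or more at 125 per arm. Some outcomes lose the primary label, and the control comparison ranks below the factorial ones, which the sponsor must accept as a choice of emphasis. Main effects are harder to read if the factors interact. With only 61% power for a 1 kg interaction, a non-significant interaction test is weak reassurance, hence the interval and cell means.
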